**1. List of abbreviations**

ART: Antiretroviral therapy

CDC: Centers for Disease Control and Prevention

GLMM: Generalized linear mixed model

HIV: Human Immunodeficiency Virus

HIV-ASES: HIV Treatment Adherence Self-Efficacy Scale

LMICs: Low-income and middle-income countries

MSM: Men who have sex with men

PLWH: People living with HIV

PI: primary investigator

RCT: Randomized controlled trial

SMS: Short message services

TPB: Theory of planned behavior

UI: User interface

WHO: World Health Organization

WHOQOL-HIV BREF: World Health Organization Quality of Life HIV short version

**2. Summary**

**Background:** The antiretroviral therapy (ART) requires a high level of adherence to ensure its effectiveness but adherence is suboptimal in many settings. Digital interventions have shown significant potential to improve ART adherence but there have been few ART interventions in China.

**Purpose:** This purpose of this study is to evaluate whether a differentiated digital intervention can improve ART adherence among men who have sex with men (MSM) living with HIV in China.

**Design:** This is a pragmatic randomized controlled trial (RCT) with two parallel arms including a baseline survey and two follow-ups with 3 months interval.

**Sites:** An infectious disease hospital (designated ART delivery site) in Jinan, Shandong Province of China

**Study populations and eligibility**: A total of 570 participants will be recruited. Eligibility criteria include MSM living with HIV who are currently on ART in the hospital, 18 years old or above, and willing to choose one of the three digital strategies (text message, only instant message or instant message plus social media group).

**Randomization**: Participants will be assigned to the intervention arm or the control arm through stratified block randomization (stratification=3, block sizes=4).

**Interventions**: The interventions include health messaging, medication reminders, peer education and online group discussion. Intervention contents are consistent but the ways of intervention delivery will be adapted based on different digital strategies.

**Study outcomes**: The primary outcome is ART adherence within the previous month. Secondary outcomes include CD4 T-cell counts, HIV detectable viral load, HIV treatment adherence self-efficacy and quality of life.

**Trial registration:** ChiCTR2000041282, retrospectively registered on 23 December 2020.

**Keywords:** Antiretroviral therapy adherence; Digital intervention; Social media; Men who have sex with men; Randomized controlled trial; China

**3. Introduction**

**3.1 Background**

Human Immunodeficiency Virus (HIV) infection remains a major public health contributor to disease burden worldwide, especially in low-income and middle-income countries (LMICs) [1, 2]. High Active Antiretroviral Therapy, introduced in mid-1990s, can effectively suppress HIV viral load and significantly reduce morbidity and mortality [3]. To ensure the effectiveness of antiretroviral therapy (ART), a high level of medication adherence (≥95%) is required [4]. However, strict adherence to a precise HIV treatment regimen has not been achieved yet in many regions. For example, a recent meta-analysis in China found that the mean rate of ≥95% adherence to ART was 81.1% at one week and dropped to 68.3% at three months or longer [5]. To achieve full adherence to avoid treatment failure, innovative approaches are needed.

Digital interventions are defined as interventions using digital technologies such as smartphones, website, and text messaging [6]. In the past decade, digital interventions have emerged as a promising solution to improve ART adherence. Particularly, short message services (SMS) interventions have been widely used due to convenience and cost-effectiveness [7-11], and are recommended by the World Health Organization (WHO) [12]. Further, social media have been used to deliver HIV interventions, especially for marginalized populations. Social media is defined as Internet-based platforms allowing the creation and exchange of user-generated contents, which usually applies mobile or Web-based technologies [13]. Studies have shown that social media can be used to promote ART adherence among key populations [14-16]. Social media offers the potential for public health practitioners to reach a larger number of people living with HIV (PLWH) and to disseminate information on sensitive topics [17]. However, most studies that focus on social media interventions were conducted in high-income countries [17]. In addition, there are few studies that have allowed people to decide which intervention they want to use, despite the known importance of preferences and people-centered approaches.

In China, there were 1,045,000 reported cases of PLWH by the end of October 2020 [18]. Among them, men who have sex with men (MSM) accounted for 23% of newly-diagnosed cases in 2019 [19]. WeChat and Tencent QQ are two of the most popular Chinese social media platform, especially for youngsters. As of 2016, WeChat had connected more than half a billion Chinese people and QQ had over 700 million active users [20, 21]. In China, there have been studies adopting social media to deliver interventions but most focused on HIV testing [13, 22, 23]. To our knowledge, only one study in South China explored the feasibility of WeChat-based intervention for ART adherence but did not observe significant improvements [24]. Another smartphone APP-based study was a protocol [25]. Few studies using digital interventions to promote ART adherence have been tested with rigorous design despite the high rates of mobile phone use [26, 27]. Therefore, we developed a differentiated comprehensive intervention which allows patients to choose different digital strategies (text message, instant message, or instant message plus social media group) based on their preferences. The differentiated intervention indicates that the ways of intervention delivery are differentiated among the subgroups.

**3.2 Objectives**

**Primary objective**: To determine if the differentiated digital intervention can improve ART adherence among MSM living with HIV at 6 months compared to the control arm.

**Hypotheses 1**: The differentiated digital intervention is superior in improving ART adherence compared to the control arm.

**Secondary objectives**: To determine (1) whether CD4 T-cell counts, HIV viral suppression, HIV treatment adherence self-efficacy and quality of life differ between the intervention arm and the control arm at 6 months; (2) whether the outcomes (i.e. ART adherence, CD4 T-cell counts, HIV viral suppression, HIV treatment self-efficacy and quality of life) differ between the two study arms within each of the three subgroups (i.e. text message subgroup, instant message subgroup, and instant message plus social media subgroup)

**Hypotheses 2**: The differentiated digital intervention is superior in improving CD4 T-cell counts, HIV viral suppression, HIV treatment adherence self-efficacy and quality of life. Text message-based intervention, instant message-based intervention, and instant message plus social media intervention are superior in improving the health outcomes.

**4. Intervention development** **and** **theoretical support**

The development of intervention was guided by the theory of planned behavior (TPB) [28] and group medical visit (or shared medical appointments) [29]. According to TPB, the most important determinant of behavior is behavioral intention. The direct determinant of one’s behavioral intention include attitude toward performing the behavior, subjective norm associated with the behavior, and perceived control over the behavior [28]. The TPB has been widely applied in sex behavior, condom use, HIV testing, and ART adherence among MSM [30-33]. Specifically, based on TPB, we plan to disseminate health messages on ART medication to strengthen behavioral beliefs about outcomes of performing the behavior, and contribute to form positive attitudes toward taking medications. Further, we will provide peer education to improve subject norm of ART adherence. An individual who believes important referents (peer educators) think he should perform a behavior and is motivated to meet expectations of the referents tends to hold positive subjective norm. Simultaneously, we will provide medication reminders and use incentives to strengthen individuals’ control belief and perceived power, and further improve perceived behavioral control. Besides, we plan to establish an online chat group to encourage discussions about ART experience based on group medical visit. The model framework of the intervention is displayed in Figure S1.

We conducted a scoping literature review on digital technologies and adherence intervention strategies. In terms of digital technologies, we found that most HIV digital interventions focused on testing and were conducted in high-income countries [13]. In terms of intervention strategies on ART adherence, we found that interventions recommended by WHO guidelines include peer counsellors, mobile phone text messages, reminder devices, and behavioral skills training et al [12]. In addition, literature showed multiple strategies were superior to a single strategy [34].

Prior to launching the study, we conducted formative research targeting MSM living with HIV in Yantai and Weifang of Shandong Province, China. We focused on the following themes: whether they had any difficulties or needs on ART at present, whether they would like to receive health services via digital platforms (and which digital platforms they would like to choose), whether they would like to join an online chat group to share ART experience with other patients (and the reasons if not). Simultaneously, we asked the health providers from local hospital and CDC about the feasibility and acceptability of implementing digital interventions among MSM living with HIV.

The final interventions include health messaging, medication reminders, peer education, and online group discussion. We will deliver interventions using different digital strategies (including text message, only instant message, and instant message plus social media group) based on patients’ preferences.

**Attitude**

Disseminating health messages about ART medication to improve attitudes to ART

**Subject norm**

Providing peer education to improve subject norm of ART adherence

**Perceived behavioral control**

Providing medication reminders and incentives to strengthen perceived behavioral control

**Group visit (inter-person level)**

Establishing an online chat group to encourage discussions about ART experience

**Behavior Intention**

Improving the behavior intention of taking ART medications

**Behavior**

Keeping consistent optimal ART adherence

TPB (individual level)

Patients’ need and preferences

Differentiated digital intervention

**Figure S1. Model framework of differentiated digital intervention**

**5. Overview of design**

This study will be a pragmatic RCT with two parallel arms designed for MSM living with HIV currently on ART. Participants will be randomly assigned in a 1:1 ratio to the intervention arm or the control arm, stratified by different digital strategies. For each stratum, block randomization will be triggered once four participants are recruited. Participants in the intervention arm will receive 6-month comprehensive interventions including ART medication messages, medication reminders, peer education and online group discussion. Participants in the control arm will receive messages on health behavior and nutrition. The study will last about 7.5 months. The first 1.5 months include the recruitment period and the baseline survey. Two follow-up surveys will be administrated every 3 months.

The flowchart of this differentiated digital intervention trial is displayed in Figure S2. The SPIRIT figure of study timeline is displayed in Figure S3.

**Figure S2. Flowchart of the differentiated digital intervention trial.**

**
[figure not shown]
**

**Figure S3. SPIRIT figure of study timeline**

**6. Trial population and study settting**

**6.1 Eligibility**

The participation eligibility criteria are: (1) HIV-diagnosed seropositive and currently on ART in the local hospital of study setting; (2) reaching 18 years old or above; (3) born biologically male and having ever had anal sex with men; (4) willing to choose one of the three provided digital strategy (text message, instant message or instant message plus social media group) and provide phone number or WeChat account (plus QQ account).

**6.2 Study setting**

The participants will be recruited from an infectious diseases hospital that serves more than 1,600 MSM patients in Jinan, Shandong Province of China.

**6.3 Recruitment**

Patients waiting to take free antiretroviral medications will be invited to a waiting room through physician referral and receive a detailed introduction of this study by trained research staff. If a patient meets the eligibility criteria, he will be asked to provide written informed consent and complete the baseline questionnaire. The treatment ID of each participant will be collected so that they can be identified in the follow-ups. In addition, based on the digital strategies they choose, participants need to provide their phone number or scan QR codes to add a WeChat account of the project as contact. For those choosing WeChat+QQ service, we will first add them as WeChat contacts, and then share QR codes to invite them to join in QQ group for some participants. The participants will be reimbursed about 7.47 USD for each of the survey questionnaire completed (including a baseline survey and two follow-up surveys).

**8. Interventions**

Participants in the intervention arm will receive interventions within six months post allocation, which include health messaging, medication reminders, peer education and online group discussion. The health messages include 12-item ART medication messages and 6-item HIV clinical messages, which are adopted from national AIDS antiviral treatment manual or authoritative websites of China’s CDC, and checked by AIDS experts from local hospital and CDCs. The 12-item ART medication messages include management of side effects, solutions for missing doses, definition of drug resistance, etc. The 6-item HIV clinical messages include explanations of some HIV terms (e.g. “window period of HIV infection”, “CD4 T-cell counts”, “HIV viral load”), precondition of ART initiation, etc. We will deliver ART medication messages every two weeks and HIV clinical messages every month respectively. Second, daily medication reminder service (SMS platform or WeChat mini-program) is designed to serve for those who need the service (optional for participants). The reminders will not include words regarding “HIV” or “AIDS” to avoid potential privacy disclosures. Third, peer education stories will be used to improve ART adherence and health perception. We will deliver peer education service every two weeks after the first follow-up (i.e. 3 months post allocation). The ways of intervention delivery are differentiated for each subgroup, the details of which are as followed.

**8.1 Text message-based intervention**

Participants will receive ART medication messages and HIV clinical messages via SMS. Besides, participants will be asked if they need daily medication reminders in the first intervention. If the response is “yes”, the daily reminders “Have you finished the task today? Remember to keep in a good mood everyday” will be sent to them about three minutes before their prescribed dose-timing via a customized SMS platform. In addition, peer education stories will be delivered to the participants via SMS after the first follow-up.

**8.2 Instant message-based intervention**

A total of 18 images of ART medication messages (n=12) and HIV clinical messages (n=6) plus six peer education videos will be delivered to participants via WeChat. The images are designed by peer volunteers from a community-based MSM organization to better attract participants (see four examples in Figure S4). In addition, we also invite peer volunteers living with HIV from a MSM organization to record six peer education videos to promote ART adherence and health perception.

[figure not shown]

**Figure S4 Four of the eighteen images of HIV clinical related knowledge and ART medication knowledge used in the intervention package**

Note: The themes of the four images from left to right are: (1) What is HIV viral load; (2) What is CD4 T-cell counts; (3) How to complement ART medications if missing doses; (4) Whether it is okay to share your own ART medications to others. Example (Left text): “What is the HIV viral load: Viral load (VL) is the number of viruses per milliliter of blood. After standardized treatment, VL will be lower than the detection limit, indicating that the virus has been effectively suppressed and the damage of the virus to body has been greatly reduced. However, undetectable viruses in blood still distribute in semen, vaginal secretions, bone marrow and internal organs, and may be transmitted to others through unsafe sex or sharing needles.”

A customized WeChat mini-program entitled “U=U” (Undetectable=Untransmittable) is developed to remind participants to take medications on time and also provide them the opportunity of online clock-punching after taking medication. WeChat mini-program, a revolutionary lightweight “APP” without the need of downloading, can significantly improve accessibility and convenience [35]. First, the research staff will send QR codes and manual of the mini-program to participants via WeChat. Those who are interested in this service can scan QR codes to authorize the login of their WeChat accounts. After that, research staff can identify them from the management platform of this mini-program and type in their ART medication information (i.e. prescribed medication time and frequency of daily medication-taking) collected from baseline questionnaire. Then the participants can enter the user interface (UI) of the mini-program (Figure S5) to complete online clock-punching. The valid time of clock-punching is limited to one hour after prescribed medication time. If the participants try to punch the clock beyond the valid time, a prompt window “Sorry, invalid clock-punching for timeout” will pop up. The participants will be awarded about 4.48 USD if they complete 30-days uninterrupted clock-punching and the reward is cumulative. A clock-punching calendar recording each participant’s own valid clock-punching dates is also available in UI of the WeChat mini-program (Figure 4). Also, participants who need daily medication reminders can receive the service delivered by this mini-program three minutes ahead of their prescribed dose-timing.

[figure not shown]

**Figure S5 The users’ interfaces (UI) of the WeChat mini program**

**8.3 Instant message plus social media group intervention**

Based on instant message-based intervention, a social media group will be established to explore the effectiveness of inter-person intervention. QQ group is one of the main functions of QQ allowing multiple users to communicate instantly. The QQ group can only be found through ID or name. Participants need to scan the QR codes shared by a team member and to receive permission of the group administrator to join the group. A team member (the group creator and administrator) and a STD physician from the hospital will be invited into this QQ group to facilitate mutual medication reminding and discussion about ART experience among participants. In addition, short articles about frontier HIV research from reliable sources (hospital, CDCs, CBOs, etc.) will be shared to this group every week.

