**8.4 Control**

For participants in the control arm, 12-item HIV health behavioral messages tailored for MSM and nutrition messages targeted HIV/AIDS patients will be delivered every two weeks via SMS or WeChat based on their choices. All of these messages are adopted from National Center for AIDS/STD Control and Prevention and National Institute for Nutrition and Health.

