**12.2 Primary analysis**

The primary analysis will be performed on an intention-to-treat analysis utilizing generalized linear mixed models (GLMMs) to evaluate the effect of the differentiated digital intervention on the primary and secondary outcomes, which will include intervention status as fixed effects and individual participants with multiple measurements as random effects. The GLMMs will adjust for the baseline outcome measures (where appropriate), stratification factors (i.e. text message, instant message, instant message plus social media group), and time (baseline, 3 months and 6 months). Baseline variables significantly associated with the outcomes and found to be imbalanced between intervention arm and control arm will also be considered for adjustment in the regression models. The risk ratio (RR) or mean difference (MD) of the outcomes between study arms will be reported as estimated intervention effects with 95% confidence intervals and two-sided P values.

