**12.5 Subgroup analysis**

Subgroup analysis by different digital strategies will be carried out to compare the primary and secondary outcomes between the study arms within each of the three strata. As we mentioned before, the sample size may not be sufficient for all three subgroups. But based on the preliminary data and sample size calculation, we can ensure sufficient power in total and at least one of the three intervention subgroups.

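### The intervention side of the third stratum shares one QQ group that the model ignores, so the stratum interval is too narrow as evidence about the social media group strategy in general

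*Protocol*

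**What the plan says.** Section 8.3 adds to the instant-message package a QQ group with one team member as creator and administrator and one physician: "a social media group will be established to explore the effectiveness of inter-person intervention". Their task is "to facilitate mutual medication reminding and discussion about ART experience among participants". The wording is singular throughout; no second group, size cap or split is described. Entry needs a QR scan and the administrator's permission, and section 6.3 says the project will "share QR codes to invite them to join in QQ group for some participants". Read with section 8.4, the invited men are the intervention arm of that stratum. Control messages "will be delivered every two weeks via SMS or WeChat based on their choices", with no group.

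Section 12.2 specifies a generalized linear mixed model, "which will include intervention status as fixed effects and individual participants with multiple measurements as random effects". It adjusts for the baseline outcome where appropriate and for "stratification factors (i.e. text message, instant message, instant message plus social media group), and time (baseline, 3 months and 6 months"). In section 12.5, the sentence that begins "Subgroup analysis by different digital strategies will be carried out to compare the primary and secondary outcomes between the study arms within each of the" goes on to name all three strata. Section 3.2 hypothesises that the text message, instant message and "instant message plus social media intervention are superior in improving the health outcomes".

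**The concern.** The QQ group is there to make its members act on one another, so their outcomes may share a common component: a lively or a silent group, or facilitators who work well or badly. Controls have no counterpart, so the dependence sits in one arm of one stratum. None of the terms in section 12.2 represents it. Participant random effects handle repeated measures on a man, and the stratum term is common to both arms.

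With one group, its particular effect cannot be separated from the effect of the strategy. At stake is the third-stratum claim in section 3.2, which concerns the strategy and not one realisation of it. The pooled comparison is touched to a lesser degree.

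**Working it through.** **Inputs.** From section 10: a difference of 0.15, two-sided alpha 0.05, power 80%, 20% loss, 190 men for the text message stratum and 190 anticipated (not guaranteed) in each of the others. From sections 5 and 7: 1:1 allocation within stratum. Not in the documents: the control rate, the ICC and the uptake of the QQ group. These are assumed below.

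**Reproducing 190.** The two-proportion formula with pooled variance under the null, at an assumed 0.80 against 0.95 (mean 0.875), is

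n = [1.960·√(2·0.875·0.125) + 0.842·√(0.80·0.20 + 0.95·0.05)]² / 0.15² = 75.1, so 76 per arm.

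Then 76/0.80 = 95 per arm and 190 in total. The plan's figure is met for independent men with no design effect. Hence m = 76 evaluable men per arm in the stratum.

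**Variance with one group.** Let k of the m intervention men join the group and share an ICC of ρ; all other men are independent. Relative to independence, the variance of the intervention-arm mean is multiplied by

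D = 1 + k(k − 1)ρ/m.

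With k = m this is the usual 1 + (m − 1)ρ. Under the null both arms have the same unit variance, so the true variance of the arm difference over the assumed one is V = (D + 1)/2. The actual error of the nominal 5% test is 2·[1 − Φ(1.96/√V)].

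Example, k = 76 and ρ = 0.02: D = 1 + 75·0.02 = 2.5; V = 1.75; 1.96/1.323 = 1.482; error 13.8%.

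Example, k = 40 and ρ = 0.02: D = 1 + 40·39·0.02/76 = 1.41; V = 1.205; 1.96/1.098 = 1.785; error 7.4%.

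**Pooled test.** With three equal strata there are 228 men per arm and D = 1 + k(k − 1)ρ/228. For k = 76 and ρ = 0.02: D = 1.5; V = 1.25; error 8.0%.

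| Assumed ICC | Stratum, all 76 join: true/assumed SE | Stratum, all 76 join: error | Stratum, 40 of 76 join: error | Pooled, all 76 join: error | Pooled, 40 of 76 join: error |
|---|---|---|---|---|---|
| 0 | 1.00 | 5.0% | 5.0% | 5.0% | 5.0% |
| 0.01 | 1.17 | 9.5% | 6.2% | 6.5% | 5.4% |
| 0.02 | 1.32 | 13.8% | 7.4% | 8.0% | 5.8% |
| 0.05 | 1.70 | 24.8% | 11.1% | 12.4% | 7.0% |

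**Check.** A beta-binomial simulation at a rate of 0.80 gave 9.6%, 14.1% and 25.8% for full uptake, and 6.2%, 7.4% and 11.1% for 40 of 76, at ICC 0.01, 0.02 and 0.05.

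**What the ICC means.** At a rate of 0.80, the group's true rate has standard deviation √(ρ·0.80·0.20): 4.0 points at 0.01, 5.7 at 0.02 and 8.9 at 0.05, against a target effect of 15 points.

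These figures come from a comparison of proportions at one time point, not from the repeated-measures model itself.

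**The case against.** A reader might infer that the stratum test is invalid. The documents do not support that. Men are randomised individually, so if the intervention changes nobody's outcome the arms are exchangeable and the test keeps its 5% level. The error rates above arise only when the null is that the strategy has no effect averaged over the groups that might have been formed. This objection stands in full: the problem is what the result can be taken to show. But section 3.2 makes its claim at the level of the strategy, so the limit matters.

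A reader might also infer that every intervention man in the stratum interacts in the group. Joining is a choice that needs permission, and much of the package reaches men individually, so full uptake is the worst case. The 40-of-76 column shows how quickly the problem shrinks. Its kind does not change.

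It is also fair to say that one hospital and one set of peer videos limit generalisation too. The QQ group differs in that it creates interaction among participants, in one arm only. Finally, the plan already softens this test: section 8.3 speaks of exploring, and sections 10 and 12.5 admit that subgroups may be too small. That warns about power. It does not warn that the interval may be too narrow.

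A last tempting step is to require several parallel groups with a partially nested model. With eight independent groups, a simulation on group means kept the error at 5.0% to 5.2%. If the same two facilitators run all eight and half the group-level variance is theirs, the error is about 7%, 9% and 15% at ICC 0.01, 0.02 and 0.05. Splitting also changes the intervention under test, and the groups may not fill.

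**Conclusion.** The point holds as a limit on the third-stratum claim. One interacting group in one arm, analysed as independent men, gives an interval that is too narrow for a statement about the social media group strategy whenever the ICC is above zero. The size rests on three assumptions that the documents do not settle: the ICC (0.01 to 0.05), the number who join, and a stratum of about 76 evaluable men per arm. That there is one group is read from consistent singular wording; no count is stated.

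The main damage is to a secondary subgroup objective. The pooled primary test is affected only mildly at the lower ICCs, and with partial uptake it stays at 7.0% or below over the whole range. Adding a QQ-group random effect to section 12.2 would not help, because one group gives no way to separate its effect from the arm effect in that stratum.

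**What to change.** - **Sections 3.2 and 12.5:** state that the third-stratum result is the effect as delivered in one QQ group and is exploratory, and make no superiority claim for the social media group strategy in general.
- **Section 12.5:** record which men joined the group. Report the third-stratum interval with the intervention-arm variance multiplied by D = 1 + k(k − 1)ρ/m, with k the number who joined, m the evaluable intervention men in the stratum, and ρ over 0.01 to 0.05. Report the pooled interval in the same way as a sensitivity analysis, with m the evaluable men in the whole intervention arm. Use k only for the variance: all men stay in the arm to which they were randomised, since joining happens after allocation.

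The cost is wording, one recorded item and a short calculation. The downside is a wider sensitivity interval and a weaker secondary claim. Several parallel groups with a partially nested model remain an optional design trade-off; they would not remove a facilitator effect common to all groups.
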